### Sample size

The study requires a total of 2700 smokers newly diagnosed with pulmonary TB (∼43 recruits from 63 TB centres, the clusters) assuming that 20% might not provide primary outcome data. This sample also includes the first 16 participants taking part in the pilot study, in case the intervention needed major refinement then we would be unable to use their data.

The required sample size for the superiority trial (phase 3) was determined by using a power of 90%, a significance level of 5% and expected abstinence rates of 18% for mTB-Tobacco and 8% for normal treatment after 6 months.^13^ The study will comprise a total of 27 TB centres, considering the ratio of intervention to control as 2:1. After considering a 20% attrition rate, it was determined that the sample size would be 704 participants. This would result in an average of around 26 individuals in each cluster. Given that the study will be carried out as a cRCT with an intracluster correlation coefficient of 0.02,^19^ the design effect was computed to be 1.50. This results in an effective sample size of around 1080 people (or 40 subjects per site).

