#### Inferential statistics

A mixed-effects model will be used to assess the impact of mTB-Tobacco on continuous outcomes, incorporating fixed effects for the intervention, random effects for clusters and relevant covariates. Logistic regression within the mixed-effects framework will be used to analyse categorical outcomes, accounting for cluster-level variability and intervention effects for the analysis of data in this cRCT. At the end of phase 3 superiority trial, an interim analysis will be done by an independent statistician to assess the effectiveness of the mTB-Tobacco intervention. The result will decide whether the trial needs to proceed to phase 4 non-inferiority trial or be terminated early. In this study, the missing data patterns will first be examined to determine whether the missingness adheres to patterns of complete randomness, randomness or non-randomness. Multiple imputation, a robust technique that generates multiple data sets with imputed values for missing observations, will be used to address the missing data. As a sensitivity analysis technique, missing data imputation will be used to evaluate the robustness of our findings.^20^ The estimates of the intervention effect will next be compared between analyses carried out with complete case analysis and analyses using imputed data sets. This will improve the validity of the study’s conclusions by enabling an assessment of the effect of missing data on the estimation of intervention effects in this cRCT. Open-source R Project software and JASP Team (2024; V.0.19.3) computer software will be employed as our primary tools for data analysis.

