Underlying uncertainty around the decision to adopt the intervention will be assessed using non-parametric bootstrap resampling technique. Bootstrapping is an efficient method for calculating the confidence limits for the ICER as its validity does not depend on any specific form of underlying distribution. We will perform the bootstrap 5000 replications and construct the 95% CIs for the ICERs based on the bootstrapping results. Cost-effectiveness acceptability curves^22^ will be constructed based on the bootstrap iterations to estimate the probability that the intervention is cost-effective at different threshold values for one QALY.

The ICER, calculated in terms of the cost per QALY, will be used to assess the value of money afforded by the intervention over and above the control and draw conclusions with respect to the potential cost-effectiveness of the intervention. To assess the impact of imputing missing data, we will also conduct a complete case analysis based on the participants who have both complete costs and QALYs at all time points, following the same analysis method as the primary analysis above. Sensitivity analyses using pattern mixture modelling will be used to examine the assumptions for multiple imputation methods.

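### The planned robustness check for month-6 abstinence cannot detect outcome-dependent dropout, and the step said to identify non-random missingness from the data cannot do so

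*Protocol article*

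**What the plan says.** All references are to the protocol article.

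- **Inferential statistics, first step.** Missing-data patterns are to be examined in order to "determine whether the missingness adheres to patterns of complete randomness, randomness or non-randomness".
- **Inferential statistics, method.** Multiple imputation "will be used to address the missing data". The next sentence gives it a different role: "As a sensitivity analysis technique, missing data imputation will be used to evaluate the robustness of our findings".
- **Inferential statistics, robustness check.** "The estimates of the intervention effect will next be compared between analyses carried out with complete case analysis and analyses using imputed data sets". The article adds that this lets the effect of missing data on the estimated intervention effect be assessed. It attaches no non-random assumption to either analysis.
- **Sample size.** The total is set "assuming that 20% might not provide primary outcome data".
- **Cost-effectiveness analysis.** After a complete-case analysis of "participants who have both complete costs and QALYs at all time points", the article states: "Sensitivity analyses using pattern mixture modelling will be used to examine the assumptions for multiple imputation methods". Nothing in the text extends this to abstinence.
- **Primary outcomes.** Verified continuous abstinence at 6 months is defined, with no rule given for a participant whose status is missing.

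**The concern.** Two statements do not do what they promise.

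First, whether missingness is random or non-random depends on the outcomes that were not seen. Patterns in the observed data can show that missingness is related to measured variables, and so is not completely random. They cannot show that nothing further depends on the unseen month-6 status.

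Second, complete-case analysis and standard multiple imputation both rest on dropout being unrelated to month-6 status given the variables used. A patient who relapses after week 9 and then avoids the month-6 visit violates that assumption in both analyses, so their agreement does not clear the result of this problem.

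The amount of missing data makes this relevant. At the planned rates, 20% of an arm is missing, while observed quitters in the mTB-Tobacco arm are 0.80 x 18% = 14.4% of those enrolled. The phase 3 result decides whether phase 4 goes ahead, and phase 4 is judged against a fixed margin of 8 points. Separately, imputation is described both as the way missing data are handled and as a sensitivity analysis, so the main analysis cannot be identified from the text.

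**Working it through.** **Inputs from the article (Sample size).** Abstinence 18% v 8% in phase 3; 18% in phase 4 with an 8-point margin; 20% missing; ICC 0.02; phase 3 with 27 centres of 40 = 1080, split 2:1 (720 and 360); phase 4 with 36 centres of 45 = 1620 (810 per arm).

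**The plan's own figures.** For phase 3, the two-proportion formula with continuity correction (two-sided 5%, 90% power, 2:1) gives 585. Then 585 x 1.2 = 702, against the stated 704. The design effects are 1 + 25 x 0.02 = 1.50 and 1 + 28 x 0.02 = 1.56, as stated. The phase 4 figure of 1036 does not reproduce at 90% power (970 before attrition); that is a separate matter. The planned totals are taken as given here.

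**Step 1: can the two planned analyses agree and both be wrong?** Suppose true abstinence is 14.4% v 8%, a difference of 6.4 points. Let 20% be missing in each arm, with all missing mTB-Tobacco patients smoking and control dropout random.
- Complete cases: 0.144/0.80 = 18% v 8%, a difference of 10.0 points.
- Imputation within arm under missing at random: 0.80 x 18% + 0.20 x 18% = 18% v 8%, again 10.0 points.

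A simulation with 2 million patients per arm gave 6.4 (truth), 10.0 (complete cases) and 10.0 (imputation).

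**Step 2: what could it do to the conclusions?** Let missing mTB-Tobacco patients abstain at k times the observed rate, with the comparator missing at random. The values of k are assumptions.
- Rate: p = 18% x (0.80 + 0.20k).
- Standard error: square root of DE x [p(1-p)/n1 + p0(1-p0)/n0], using observed numbers.
- Phase 3: n = 576 and 288, 32 observed per centre, DE = 1 + 31 x 0.02 = 1.62.
- Phase 4: n = 648 and 648, 36 observed per centre, DE = 1 + 35 x 0.02 = 1.70.
- Lower limit: difference minus 1.96 standard errors.

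| k | Phase 3 difference | Phase 3 lower limit | Phase 4 difference | Phase 4 lower limit (margin -8) |
|---|---|---|---|---|
| 100% | 10.0 | 4.4 | 0.0 | -5.5 |
| 50% | 8.2 | 2.7 | -1.8 | -7.1 |
| 25% | 7.3 | 1.8 | -2.7 | -8.0 |
| 0% | 6.4 | 1.0 | -3.6 | -8.8 |

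For example, phase 4 at k = 0: p = 14.4%; SE = square root of 1.70 x (0.144 x 0.856 + 0.18 x 0.82)/648 = 2.67 points; lower limit -3.6 - 1.96 x 2.67 = -8.8.

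**Step 3: all missing smoke, with equal or unequal dropout** (rate = observed rate x fraction observed).

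| Missing, mTB-Tobacco v comparator | Phase 3 | Phase 4 |
|---|---|---|
| 20% v 20% | 14.4% v 6.4% = 8.0 | 0 |
| 25% v 15% | 13.5% v 6.8% = 6.7 | 13.5% v 15.3% = -1.8 |
| 15% v 25% | 15.3% v 6.0% = 9.3 | 15.3% v 13.5% = +1.8 |

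With equal 20% dropout the odds ratio barely changes: (0.18/0.82)/(0.08/0.92) = 2.52 against (0.144/0.856)/(0.064/0.936) = 2.46.

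**The case against.** **The full documents are not shown.** The article condenses an approved protocol, and shift ranges and scenario sets are commonly left to an analysis plan. A reader might infer that the trial has no test of non-random dropout for its primary outcome. The article cannot support that; it shows only that none is stated here. What remains is a statement that is wrong as written and a named check that cannot do its stated job.

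**The outcome standard might settle it.** The abstract defines abstinence per the Russell Standard. Whether that standard sets a rule for missing status is not in the article, and the section on missing data prescribes imputation. The point does not rely on it either way.

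**Imputation may use more than arm.** Smoking status and nicotine dependence are collected at week 9, and TB outcomes come from the register. Imputation using these could pick up early relapse and differ from complete cases. It would be too strong to say that agreement between the two carries no information. Only dependence on month-6 status beyond such predictors escapes, and Step 1 shows the extreme case.

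**The direction is unknown.** A reader might infer that the bias must favour mTB-Tobacco. The Weekly monitoring calls section describes calls about receiving and reading the messages, so apparently to the SMS arm, and expects them to help follow-up. That could mean less missing data in that arm, and Step 3 shows the effect reversing.

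**The shifts may be severe.** The Introduction cites an odds ratio of 1.35 for loss to follow-up in smokers with TB. With 18% true abstinence and 20% missing overall, that ratio gives missing risks of about 16.3% in abstainers and 20.8% in smokers (0.18 x 16.3% + 0.82 x 20.8% = 20%). Observed abstinence is then 0.18 x 0.837/0.80 = 18.8%, a bias of 0.8 points, which is milder than the 50% row. This stands: the lower rows are stress values, not forecasts.

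**The classification step has no stated consequence.** This is true. Imputation and complete cases follow whatever it finds, so rewording it changes no estimate.

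**Conclusion.** The point holds in limited form. The article claims to learn from observed data something they cannot show. Its only stated robustness check for abstinence compares two analyses that share the vulnerable assumption.

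The practical weight falls on phase 4. On the planned sizes, non-inferiority is borderline when missing mTB-Tobacco patients abstain at a quarter of the observed rate, and is lost when none abstain, while both planned analyses could still show about no difference. It would be wrong to infer that the phase 3 conclusion is fragile: under the same shifts its lower limit stays above zero, and with equal dropout the odds ratio is almost unchanged.

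These sizes rest on the design-stage rates, 20% missing, ICC 0.02, a comparator missing at random, assumed abstinence among the missing, and a risk-difference approximation in place of the planned mixed logistic model. They show what the stated check could miss, not what will happen.

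**What to change.** 1. Reword the classification step: describe the amount of missingness and its observed predictors by arm, and drop the claim to establish the mechanism.
2. Name one main analysis for month-6 abstinence, and say whether multiple imputation is that analysis or a sensitivity analysis.
3. Keep the complete-case comparison if wanted, but do not let it stand alone as the robustness check.
4. Extend the pattern-mixture approach already planned in the economic section to month-6 abstinence. Use arm-specific shifts from missing at random to all missing smoking, with either arm allowed the larger shift.
5. Report tipping points against zero in phase 3 and against the 8-point margin in phase 4.

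The cost is some wording and a few more model runs, with no new data. The downside is a possibly less favourable robustness statement, mainly in phase 4.

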#### Cost-effectiveness analysis

Health economic evaluation will be conducted to establish the value for money afforded by the mTB-Tobacco intervention. The cost of providing the interventions will be recorded and calculated using local cost data. Costs include staff, premises and pharmaceutical products. Patients’ wider use of public and private healthcare will also be recorded, using a self-report service use questionnaire. Patient cost profiles will be calculated by applying country-specific unit cost tariffs to quantities. Total intervention cost, costs of wider healthcare use and also patients’ out-of-pocket expenditure will be derived, and a total cost will be applied to each patient in each trial arm.

In the superiority trial (phase 3), an incremental cost-effectiveness analysis (CEA) of the mTB-Tobacco intervention will be conducted, over and above usual care. European Quality of Life 5-dimensions 5-levels (EQ-5D-5L) questionnaire will be used to calculate quality-adjusted life years (QALYs) using the area under the curve.^21^ Incremental cost-effectiveness ratios (ICERs) will be presented in terms of (1) cost per QALY and (2) cost per additional quitter as based on the secondary outcome of the trial. A 12-month time horizon is selected for the CEA to use the longer-term window of healthcare use and changes in health-related quality of life. A full sensitivity analysis will be presented to assess the robustness of the results and the probability that mTB-Tobacco intervention is cost-effective at a range of threshold values.

In a non-inferiority trial (phase 4), resource quantities and attribute unit costs will be recorded for the mTB-Tobacco intervention and face-to-face behaviour support, inclusive of wider health system costs following the methodology of the phase 3 superiority trial. Costs for each arm will be calculated and compared with a predefined acceptable cost difference. A CEA will also be done for the non-inferiority trial (phase 4). Differences in costs and QALYs between treatment arms will be estimated to calculate the ICER for the cost per QALY and cost per additional quitter.

Underlying uncertainty around the decision to adopt the intervention will be assessed using non-parametric bootstrap resampling technique. Bootstrapping is an efficient method for calculating the confidence limits for the ICER as its validity does not depend on any specific form of underlying distribution. We will perform the bootstrap 5000 replications and construct the 95% CIs for the ICERs based on the bootstrapping results. Cost-effectiveness acceptability curves^22^ will be constructed based on the bootstrap iterations to estimate the probability that the intervention is cost-effective at different threshold values for one QALY.

The ICER, calculated in terms of the cost per QALY, will be used to assess the value of money afforded by the intervention over and above the control and draw conclusions with respect to the potential cost-effectiveness of the intervention. To assess the impact of imputing missing data, we will also conduct a complete case analysis based on the participants who have both complete costs and QALYs at all time points, following the same analysis method as the primary analysis above. Sensitivity analyses using pattern mixture modelling will be used to examine the assumptions for multiple imputation methods.

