**Figure 1 F1:**
[figure not shown]
Study design and phases of the Quit4TB trial. PPI, patients and public involvement; TB, tuberculosis.

Phase 2 consists of a pilot study, which aims to assess the feasibility of the mTB-Tobacco intervention and other trial processes. The mTB-Tobacco web-based intervention will be pilot tested with a total of 16 participants, 8 each from Bangladesh and Pakistan, that is, 4 in the intervention and 4 in the control arm, in each of Bangladesh and Pakistan. The pilot data will be evaluated using two sets of data, users’ self-reported experiences and their real-time engagement with the programme. Users’ experiences will be collected at a 9-week follow-up through face-to-face interactions. Key questions will focus on users’ experience of taking part in the mTB-Tobacco programme; the clarity, quantity, timing and frequency of messages; what was good about the programme and what was not; completion or non-completion of the programme; and any effect on their attitudes or target behaviour(s). Users’ real-time engagement will be evaluated using computer records from the programme used for launching mTB-Tobacco. The pilot study will be embedded in the next phase of the study, by continuing the pilot study participant’s follow-up up to 6 months, and will be treated with the same processes and governance as the main trial participant data.

Phase 3 will be the superiority trial, which will last for 12 months (6 months recruitments and 6 months follow-ups), to assess effectiveness and cost-effectiveness of mTB-Tobacco (intervention A) compared with usual care (control).

Phase 4 will be the non-inferiority trial that will be conducted if in phase 3 the mTB-Tobacco intervention turns out to be effective in helping patients with TB quit smoking as compared with control. Phase 4 will then last for another 12 months (6 months recruitment and 6 months follow-ups) to compare mTB-Tobacco (intervention A) with the face-to-face behavioural support (intervention B) to assess if it’s as effective as the face-to-face behavioural support intervention to help patients with TB quit smoking. All new patients with TB will be enrolled in phase 4, none of whom will be previously enrolled in phase 3 of the trial.

The trial flow chart is given in figure 2, followed by a written explanation of various aspects of the trial.

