#### Secondary outcomes

The secondary outcomes include: point abstinence, defined as a self-report of not using tobacco in the previous 7 days, assessed at week 9 and month 6; Adherence to TB treatment: All registered patients with TB’s medication logs (for anti-TB medication) are recorded on the ‘Treatment Support Card’; a copy of this card would be requested from the TB paramedic by the RA and attached with the patient CRF; TB Programme outcomes: the proportion of treatment success (including cured and completed treatment), treatment failure, defaulted and died will be recorded from the TB register (TB03) at month 6; and Economic evaluation. Table 1 gives definitions of TB treatment outcomes.

**Table 1 T1:** Definitions of TB treatment outcomes as per guidelines

Sr. no.	TB treatment outcomes	Definition
1	Cured	A patient who was initially smear-positive and who was smear-negative in the last month of treatment (at month 6) and on at least one previous occasion.
2	Completed treatment	A patient who completed treatment (at month 6) but did not meet the criteria for cure or failure.
3	Treatment failure	A patient who was initially smear-positive and who remained smear-positive at month 6 or later during treatment.
4	Defaulted	A patient whose treatment was interrupted for two consecutive months or more.
5	Died	A patient who died from any cause during treatment.
6	Relapse	A patient who was previously treated for TB, was declared cured or treatment completed at the end of his most recent course of treatment and is now diagnosed with a recurrent episode of TB (either a true relapse or a new episode of TB caused by reinfection).

TB, tuberculosis.

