### Study assessments

All study participants will have assessments on day 0, week 9 and month 6 time points corresponding with routine TB clinic visits. All the trial activities will be performed by field RAs (one RA per site) who will be hired and trained to take patient consent, collect baseline data, follow-up data and perform study assessments. The trial assessment schedule, given as table 2, outlines the visit dates necessary for data collection, but the patient may be seen more frequently for routine clinical care as needed. During the treatment period, if study participants are unable to attend on the day, every effort would be made to complete the visit within 2 days of the scheduled date. If a scheduled visit is missed without notice, then the RA should endeavour to contact the patient by phone or by home visit.

**Table 2 T2:** Participant enrolment and follow-up assessment schedule for Quit4TB trial

Assessment	Screening	Day 0 baseline	Week 9	Month 6
Assessment of eligibility criteria	⌧			
Written informed consent	⌧			
Face-to-face/phone-based interaction			⌧	
Self-reported tobacco use/abstinence status		⌧	⌧	⌧
CO measurement				⌧
Sociodemographic information		⌧		
Tobacco use and quit history		⌧		
Nicotine dependency		⌧	⌧	⌧
Economic outcomes		⌧		⌧
Process outcomes (fidelity)			⌧	⌧
Medication (TB) compliance			⌧	⌧
Adverse events review			⌧	⌧
TB outcomes				⌧

CO, carbon monoxide; TB, tuberculosis.

During the follow-up phase, scheduled assessments will be carried out no more than 5 days before the scheduled visit. Scheduled visits will be rescheduled to allow for public holidays or other unavoidable circumstances that affect the scheduled visit date, but the rescheduled visit should be no more than 5 days from the originally scheduled visit date. Participants will also be given a card with the contact details for the trial RA and the clinical TB care team at their site. If a patient is more than 5 days late for a scheduled study visit, an additional visit will be performed as soon as possible, including the appropriate assessments that were specified in the trial schedule for the visit that was missed.

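### The cost-effectiveness analysis sets a 12-month horizon although economic data stop at month 6, and its quitter appears to be the unverified secondary outcome rather than the verified primary one

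*Protocol article*

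**What the plan says.** On the horizon, the Cost-effectiveness analysis section of the protocol article states, for phase 3: "A 12-month time horizon is selected for the CEA to use the longer-term window of healthcare use and changes in health-related quality of life". QALYs come from the EQ-5D-5L by area under the curve, and wider healthcare use from a self-report questionnaire. Phase 4 is to follow the phase 3 costing methods and also yields a cost per QALY.

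On the data, the Study assessments section states: "All study participants will have assessments on day 0, week 9 and month 6 time points". Table 2 there marks economic outcomes at day 0 and month 6 only. The Trial design section describes phase 3 as a trial "which will last for 12 months (6 months recruitments and 6 months follow-ups") and adds: "Phase 4 will then last for another 12 months (6 months recruitment and 6 months follow-ups"). Phase 4 enrols new patients only, "none of whom will be previously enrolled in phase 3 of the trial". Under Trial status, phase 3 is analysed once the last participant has had the 6-month visit.

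On the quitter, the economic section specifies "cost per additional quitter as based on the secondary outcome of the trial" and does not name that outcome. Among the secondary outcomes, the one abstinence measure is point abstinence, "defined as a self-report of not using tobacco in the previous 7 days", taken at week 9 and month 6. The primary outcome is continuous abstinence at month 6 verified by breath CO (plus urine cotinine in those who also use smokeless tobacco), and a contrary biochemical result overrides what the participant reports.

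**The concern.** An area under a utility curve needs utilities across the period it covers, and a 12-month cost needs resource use over 12 months. The reason given for choosing 12 months is to capture healthcare use and quality-of-life change over a longer window, which reads as something observed. The schedule observes neither after month 6. Cost per QALY is the measure from which the article will draw its conclusion on cost-effectiveness, so that conclusion would depend on an assumption the article does not state.

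The second issue is consistency of the effect measure. Participants know whether they receive messages (Blinding section), so self-reported quitting can be biased differently in the two arms. The primary outcome guards against this by verification. If the economic analysis counts self-reported 7-day quitters, a person whom the primary outcome classes as a tobacco user can count as a quitter in the cost-effectiveness ratio.

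**Working it through.** **Horizon against schedule**

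| Item | Value | Source |
|---|---|---|
| Stated horizon | 12 months | Cost-effectiveness analysis |
| Last economic assessment | month 6 | Table 2 |
| Follow-up per participant, phases 3 and 4 | 6 months | Trial design |
| Phase 3 participants followed on in phase 4 | none | Trial design |
| Phase 3 analysis | after the last 6-month visit | Trial status |

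Table 2 does not list the EQ-5D-5L separately; I take it to fall under economic outcomes. The conclusion does not depend on this, because no row has a visit after month 6.

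Share of the horizon observed = 6/12 = 50%. The figure of 12 months can be reproduced only as calendar time for a phase: 6 (recruitment) + 6 (follow-up) = 12. It cannot be reproduced as time under observation for a participant.

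**What the unobserved half can do to the QALY difference**

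The article gives no expected utility difference, so I assume a between-arm difference of 0 at baseline and 0.05 at month 6, with time in years.

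- Observed part: 0.5 × (0 + 0.05)/2 = 0.0125 QALYs.
- Months 6 to 12: 0.5 × (0.05 + d12)/2, where d12 is the assumed difference at month 12.

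| Assumption after month 6 | Added | 12-month total | Multiple of observed |
|---|---|---|---|
| Difference vanishes at once | 0 | 0.0125 | 1 |
| Fades linearly to 0 | 0.5 × (0.05 + 0)/2 = 0.0125 | 0.0250 | 2 |
| Carried forward at 0.05 | 0.5 × (0.05 + 0.05)/2 = 0.0250 | 0.0375 | 3 |
| Trend continues to 0.10 | 0.5 × (0.05 + 0.10)/2 = 0.0375 | 0.0500 | 4 |

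The multiples do not depend on the value 0.05, but they do depend on a zero difference at baseline. If incremental cost were the same under all four assumptions, the 12-month cost per QALY would be 1, 1/2, 1/3 or 1/4 of the 6-month figure.

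**Which quitter**

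The secondary outcomes are point abstinence, adherence to TB treatment, TB programme outcomes and the economic evaluation itself. Only point abstinence counts quitters. It differs from the primary outcome in three ways:

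- It has no biochemical verification.
- It covers 7 days rather than the time since the quit date.
- It is assessed at two time points, and the economic section does not choose between week 9 and month 6.

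Table 2 schedules CO measurement at month 6, so a verified count will exist for the same participants.

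**The case against.** The strongest defence is that a horizon may properly exceed follow-up when an extrapolation is specified, and that the article condenses a fuller protocol (version 5.0) which is not shown. This stands in part: a reader might infer that a 12-month QALY cannot be calculated at all, or that modelled values will be passed off as trial data, and the text supports neither. It does not remove the contradiction, because the reason given for 12 months describes a window of use and quality of life that the printed schedule does not observe. A reader might also infer that 12 months was carried over from the length of a phase. The numbers coincide, but the article does not say so, and the point does not need it.

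On the quitter, the economic section does not name the outcome, so self-reported 7-day abstinence is an inference. It could be a slip for the primary outcome. As written, however, no other secondary outcome counts quitters. A reader might go further and expect the cost per quitter to conflict with the main trial result; nothing in the document shows that it will.

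Two further inferences should be resisted. The plan to "construct the 95% CIs for the ICERs based on the bootstrapping results" does not state the resampling unit, so the document gives no ground for saying that clustering is ignored; that detail may properly sit in an analysis plan, and any figure for lost coverage would need an intracluster correlation for costs and QALYs that the article does not give. Nor is the instability of a ratio interval when the effect difference is near zero a defect here: the section also plans acceptability curves over a range of thresholds and, in phase 4, a comparison of costs with a predefined acceptable difference.

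**Conclusion.** Both parts hold. The 12-month horizon contradicts the 6-month schedule printed in the same article: 50% of it is without data for every participant, and no method is given to fill the gap. Under the four simple assumptions above, the QALY gain ranges from 1 to 4 times the observed gain; this illustrates scale and is neither a forecast nor a bound. The outcome behind cost per additional quitter is unnamed, its time point is open, and on the only reading the text supports it is an unverified self-report in an open-label trial. That reading is an inference and should be labelled as one. The point affects the economic objective, not the primary clinical comparison, and it should be corrected before the economic analysis is run.

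**What to change.** 1. Set the within-trial base-case horizon to 6 months, matching Table 2. Label any 12-month result as a modelled extrapolation, state its assumptions about costs and utilities after month 6, and vary them at least across the cases tabulated above. Say that the same rule applies to phase 4.
2. Base cost per additional quitter on the primary outcome, CO-verified continuous abstinence at month 6. Report the self-reported 7-day measure as a sensitivity analysis, with its time point named.

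Both are changes of wording and need no new data. The cost is a smaller base-case QALY gain wherever a benefit would have persisted beyond month 6 and, unless later cost differences offset it, a less favourable cost per QALY.

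The alternative, an added economic assessment at month 12, would give the stated horizon real data but needs further follow-up. Reading the Trial status section as 6 months of recruitment from February 2024, the last phase 3 participant would reach month 12 in about August 2025, after the stated study end of June 2025.
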